# VERSION DATE: 08/19/2022

# Study Summary:

| Investigational Agent(s)  (Drugs or Devices) | N/A |
| --- | --- |
| IND / IDE / HDE # | N/A |
| Indicate  Special Population(s) | Children  Children who are wards of the state  Adults Unable to Consent  Cognitively Impaired Adults  Neonates of Uncertain Viability  Pregnant Women  Prisoners (or other detained/paroled individuals)  Students/Employees |
| Sample Size | 240 |
| Funding Source | Patrick G. & Shirley W. Ryan Foundation |
| Indicate the type of consent to be obtained | Written  Verbal/Waiver of Documentation of Informed Consent  Waiver of HIPAA Authorization  Waiver/Alteration of Consent Process |
| Site | Lead Site (For A Multiple Site Research Study)  Data Coordinating Center (DCC) |
| Research Related Radiation Exposure | Yes  No |
| DSMB / DMC / IDMC | Yes  No |

# Objectives:

Project Corbett is a randomized controlled trial to evaluate the efficacy of a one-year long, evidence- and clinical experience-based intervention to improve motor function and reduce the severity of motor delays in infants who have been admitted to a Neonatal Intensive Care Unit (NICU). We will also assess movement impairments and function using outcome measures at various time points up to 24-months corrected age.

# Study Aims:

*Pilot study*: Due to the large recruitment goal and length of the project, the study team/PIs will evaluate the first cohort of 6-10 participants to refine study procedures and study-related materials. If no major modifications are made to the protocol as a result of this evaluation, data from these participants will be included for analysis.

*Aim 1****:*** Evaluate the efficacy of an early, evidence-based, clinical experience–based therapeutic intervention (from the NICU to 12-months corrected age) on improving motor function and reducing severity of motor delays in infants at 12-months corrected age.

Primary Outcome Measure:

Bayley-4 Motor Score at 12-months corrected age

*We hypothesize that the intervention group will demonstrate an average 8-point difference (0.5 standard deviation) compared to the standard of care group. [an 8-point difference is considered a clinically meaningful difference]*

*Aim 2*: Evaluate the early effects (i.e., before 12 months) of a therapeutic intervention, provided from NICU to 12-months corrected age, on motor function and severity of motor delay.

*We hypothesize that a statistically significant higher percentage of infants in the intervention group will demonstrate improved motor function and reduced severity of motor delays, compared to the standard of care group—assessed using sensors,* *the NSMDA and TIMP—as early as 3-months corrected age.*

*Aim 3*: Evaluate whether an early intervention that focuses on caregiver engagement improves caregiver well-being.

*We hypothesize that an intervention that focuses on supporting and addressing the individual needs of the caregiver will improve caregiver well-being. We will evaluate these effects using the PedsQL (Family Impact Module).*

**Background**:

Infants with typical neuromotor development exhibit so-called *general movements* (GMs), which are initiated by central pattern generators in the spinal cord or brain stem and modulated by the developing supraspinal circuitry. GMs evolve naturally during development, based on ongoing development of the brain. In pre-term and term infants, GMs are characterized by whole-body movements that vary in sequence, amplitude, and speed. Until 36-38 weeks post-menstrual age (PMA) these movements involve many movements of the trunk. After 38 weeks, GMs have more of a *writhing* quality, in which movement of the trunk is less obvious and movements become slower and smaller in amplitude. Between approximately 9 and 17 weeks post term, GMs are characterized by small movements in all directions that vary moderately in speed and acceleration—called *fidgety* movements. Fidgety movements are most prominent between 11-16 weeks post-term and disappear around 5 months post-term as they are gradually replaced by goal-directed, intentional, antigravity movements such as reaching.

Because the evolution of GMs in typically developing infants represents ongoing phases of motor development, atypical motor patterns in infants (i.e., as evaluated by the General Movement Assessment [GMA] or the Hammersmith Infant Neurological Examination [HINE]) in infants may reflect impaired motor development due to discrete clinical conditions (e.g., cerebral palsy, genetic disorders, autism spectrum disorder, or minor neurological dysfunction [MND]) or overall neuromotor delay. These conditions are highly associated with known risk factors, such as pre-term birth or damage to specific areas of the brain, which interrupt or disrupt these developmental processes.

Early theories regarded motor development as an innate, natural process. However, recent theories suggest that motor development progresses through phases that are affected variously by experiences, genes, and epigenetics. Abundant variability in movement in the typically developing infant provides rich self-produced sensory and proprioceptive feedback that in turn facilitates motor development. In later stages, this feedback information can be increasingly used to coordinate self-initiated, goal directed motor behavior; the typically developing infant is able to select from a wide repertoire of possible movements to accomplish a desired task. The infant can learn from their own movements as well as by imitating movements of others due to neural mirror networks that are already present at birth. Goal-directed movements develop sequentially, corresponding to different phases of development; e.g., postural adjustments emerge after 3 months, and reaching activities develop between 6-15 months. During these adaptive phases, the infant can increasingly incorporate sensory feedback from the environment in order to fine-tune intended movements.

Because of the high plasticity of the infant brain, early intervention may be an important strategy to overcome or minimize impairments resulting from early brain damage. Because development relies on sensory feedback—obtained through active movement and interaction with the environment and other individuals—opportunities for self-directed movement (active learning), environmental enrichment, and caregiver engagement are key intervention components. In addition, for infants at risk of neurodevelopmental delay, empowering caregivers through positive communication, focusing on achievement rather than impairment, may improve caregiver wellbeing, thus facilitating improved interactions between parent and infant.

The proposed intervention is therefore based on five principles: active learning, caregiver engagement, environmental enrichment, strengths-based communication between the therapist and caregiver that focuses on the achievements of the individual infant, and dose. In addition, the intervention starts as early as possible (in the NICU) to capitalize on neuroplastic potential, comprises a high-dose of therapist- and parent-delivered activities, and continues until 12-months corrected age to enable continued functional progression throughout the first year of life.

# Study Endpoints:

*Primary Study Endpoints:*

- Completion of the 12-month assessment time-point for up to 240 infants, across all sites.
- Analysis of the Bayley-4 motor scores at the 12-month testing time-point for up to 240 infants, across all sites.

*Secondary Study Endpoints:*

- Evaluation of whether the intervention results in a reduction in the severity of motor delays, compared to the standard of care group, that can be detected as early as 3-months corrected age.
- Evaluation of the intervention’s impact on caregiver health-related quality of life.

# Inclusion and Exclusion Criteria

## Screening

Infants admitted to the NICU will be screened by study team members at each respective recruitment site starting at 33-34 weeks PMA. They will be identified as appropriate for the study based on the following inclusion/exclusion criteria. Screening will be completed with an electronic medical record review. Families will not be approached by study staff until the infant is medically stable and the family has been cleared by the NICU staff as ready to approach.

## Infants

*Inclusion criteria*

NICU admission and qualifies for Early Childhood Clinic (NICU high-risk follow up clinic) or Early Intervention due to:

- BW <1500 grams

**OR**

- Disorders of the central nervous system

—Brain injury (including but not limited to extra axial hemorrhage, any grade intraventricular or intraparenchymal hemorrhage, stroke, hypoxic ischemic encephalopathy (HIE), meningitis)

- - HIE includes mild, moderate, severe exam on modified Sarnat exam, both cooled and non-cooled
  - includes “*at* *risk for HIE”* with 10-minute Apgar <7 plus pH<7.15 or base deficit >/=12.

—Brain developmental abnormalities (hydrocephalus, microcephaly, cortical dysgenesis)

—Cramped synchronous movements at term PMA

**OR**

- Bronchopulmonary dysplasia (BPD) defined as need for respiratory support at 36 weeks postmenstrual age in an infant born at <32 weeks of gestation.

**AND**

- Medically stable **AND** able to start intervention between 34-48 weeks PMA.

*Exclusion criteria:*

(related to inability to complete intervention, sensor placement, or clinic assessments)

- open wounds, skin condition precluding sensor placement
- immune deficiencies requiring protective isolation
- limb reduction defects
- Followed primarily in another clinic (including but not limited to meningomyelocele and related conditions/trisomy 21)
- bleeding disorders or ongoing need for anticoagulation
- palliative or hospice care (for life limiting conditions including, but not limited to trisomy 18, 13)
- known visual impairment at the time of enrollment
- DCFS custody
- No English-speaking caregivers
- Any other condition that would preclude participation in the study, as determined by the PI
- Previously enrolled in competing randomized trial with developmental outcome variables

Each child’s enrollment in the study will be approved by the child’s neonatologist.

Standard of care therapists

*Inclusion Criteria:*

- Therapist treating an infant enrolled in the study post-NICU, in either the standard of care group or the intervention group.

*Exclusion Criteria:*

- ​Not treating infant involved in the study

# Study Intervention(s)/ Investigational Agent(s):

***Summary:***

Project Corbett is a randomized controlled trial evaluating the efficacy of a one-year long, evidence- and clinical experience-based intervention to improve motor function and reduce the severity of motor delays in infants admitted to the Neonatal Intensive Care Unit (NICU). Eligible infants will be enrolled during their NICU stay. Randomization will be stratified based on the infant’s risk of neuromotor delay. Infants randomized to the intervention group will complete up to two visits per week and will be provided a set of worksheets and videos (the Activity Playbook) to promote functional progression. Parents will be asked to complete activities described in the Activity Playbook for at least 20 minutes per day 5 days per week, which will be progressed collaboratively between the therapist and caregiver. Infants randomized to the standard of care group will receive services as deemed appropriate by their supervising medical team. Both groups will be able to seek out and receive therapy or medical services outside of the study, without limitation; however, the study team will aim to monitor the frequency and dosage of any additional services received. All enrolled participants, regardless of group allocation, will complete assessments at defined time-points (shown in Table 1), up to 24-months corrected age.

***Intervention Group:***

The intervention will start in the NICU and continue for up to 12-months corrected age. It is divided into 3 blocks:

- **Block A** is defined as the period from enrollment until discharge from the NICU.
- **Block B** is defined as post-NICU until 3-months corrected age.
- **Block C** is defined as 3-months until 12-months corrected age.

All intervention sessions within each of the blocks will focus on providing a high dosage of intervention while incorporating a strengths-based approach that focuses on the principles of active learning, environmental enrichment, and caregiver engagement. Infants in the intervention group may also receive services as assigned by their managing care providers, including referral to Early Intervention or outpatient therapy services. Participants will not be prevented from receiving any service that they would otherwise be eligible for as a result of participation in this study. Study staff will monitor the frequency and type of additional services received using parent surveys. We will provide participants with contact information for study staff.

***Block A (NICU to discharge home):***

Participants will receive 1-2 visits per week in the NICU (with option for telemedicine for parent participation, if needed) based on infant status and tolerance. Primary goals of Block A will be to:

- Build caregiver competency in infant signal and stress cue management.
- Maximize and support caregiver confidence in infant interactions.
- Introduce variable positions to promote caregiver engagement and infant tolerance to movement.
- Promote active learning in different functional positions.

Intervention therapists will provide caregivers with written and video resources (the Activity Playbook), based on the infant’s abilities and tolerance, to promote functional progression. Intervention therapists may also provide supplementary materials related to infant state regulation, additional activities, and/or caregiver bonding, as necessary.

Activity recommendations will address the goals outlined above. Activities will be progressed appropriately by the intervention therapist and caregiver(s), based on collaboratively identified goals, caregiver needs, and the infant’s functional progression.

Caregivers will be asked to complete the Activity Playbook assigned by the intervention therapists at a target dosage of at least 5 days/week for at least 20 minutes per day. Caregivers will be asked to track the amount of time they spent on the activities.

Study staff will monitor caregiver engagement and intervention therapists will assist with any barriers to implementation of the Activity Playbook. Intervention therapists will communicate with the study medical team if they become aware of any additional needs that fall out of the scope of the study.

***Block B (post-NICU to 3-months corrected age) and Block C (3-months to 12-months corrected age):***

Participants will be provided with two in-person intervention sessions per week within their homes (in-clinic or telemedicine options may be available, if necessary).

Primary goals of **Block B** will be to:

- Build caregiver competency in infant signal and stress cue management.
- Maximize and support caregiver confidence during infant interactions.
- Introduce variable positions to promote caregiver engagement and infant tolerance to movement.
- Promote active learning in different functional positions.
- Collaborate with caregivers to facilitate integration of Activity Playbook recommendations throughout their day.

Primary goals of **Block C** include:

- Promote active learning in varied positions while progressing goal-directed behaviors.
- Collaborate with caregivers to maximize competency and consistency in completing Activity Playbook recommendations at recommended dosage.

Throughout the intervention session, intervention therapists will work with caregivers to progress infant motor development and facilitate goal-directed behaviors.

Intervention therapists will promote active participation of caregivers, while focusing on integration of the study principles.

Caregivers will be asked to complete Activity Playbook recommendations assigned by the intervention therapists at a target dosage of at least 5 days/week for at least 20 minutes per day. The therapist and caregivers will collaboratively progress the target dosage.

Intervention sessions and Activity Playbook recommendations will be modified appropriately by the intervention therapist, based on collaboratively identified goals, caregiver needs, and functional progression of the infant.

Study staff will monitor caregiver engagement and intervention therapists will assist with any barriers to implementation.

As a smartphone or other device (e.g., laptop, tablet) will be required to access videos and some study surveys, we will provide a smartphone and data plan to caregivers in the Intervention group, if necessary, until they complete the study (approximately 12-months corrected age).

Sensor data may be acquired during intervention sessions to evaluate infant movement. These sensors are described in the assessment section below.

***Assessment Timeline:*** Assessments will be completed at study enrollment and thereafter at monthly intervals up to 3 months corrected age, then at 3-months corrected age, 6-months corrected age, 9-months corrected age, 12-months corrected age, 18-months corrected age (optional), and 24-months corrected age (optional). The number of assessments prior to 3 months corrected age will vary by preterm status and age of enrollment. Optional assessments will be completed if (i) the study is still ongoing and (ii) the caregiver agrees to do so. If infants are unable to complete any required assessment sessions, an attempt to re-schedule will be made. If infants are unable to complete a testing session, their participation in the study will not be affected; however, the study team will appropriately document the missing data.

***Additional monitoring:*** Intervention therapists and study team members will monitor infant response to intervention sessions, caregiver engagement (caregiver- and therapist-report) compliance to key principles, percentage of intervention sessions completed, the dosage of Activity Playbook activities achieved (caregiver report), any adverse events/changes in medical status, additional services received outside of study participation, general medical and health updates, and additional information if relevant for study purposes. Surveys or medical chart reviews may be utilized to capture the above information throughout study participation.

***Standard of Care Group:***

Participants will receive services as assigned by their clinical team. Families will receive information on early intervention services, including speech therapy, occupational therapy, and/or physical therapy. The child will be referred by the clinical team, if eligible, and the family is interested in these services. Participants will not be prevented from receiving any service that they would otherwise be eligible for as a result of participation in this study. Study staff will monitor the frequency and type of additional services received.

For all participants, we will monitor access to recommended services and follow up if families report having difficulty accessing desired services and would like assistance. We will provide all participants with contact information for study staff.

*Assessment Timelin****e:*** Assessments will be completed at study enrollment and thereafter at monthly intervals up to 3 months corrected age, then at 3-months corrected age, 6-months corrected age, 9-months corrected age, 12-months corrected age, 18-months corrected age (optional), and 24-months corrected age (optional). The number of assessments prior to 3 months corrected age will vary by preterm status and age of enrollment. Optional assessments will be completed if (i) the study is still ongoing and (ii) the caregiver agrees to do so. If infants are unable to complete an assessment session, we will attempt to reschedule the appointment. If the infant does not complete an assessment session, their participation in the study will not be impacted; however, the study team will appropriately document the missing data.

*Additional monitoring:* Study team members will monitor for any adverse events/changes in infant medical status, general medical and health updates, and therapy services received outside of study participation. Additional information may be collected, if relevant for study purposes. Surveys or medical chart reviews may be utilized to capture the above information throughout study participation.

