*Home:* The Block B and C intervention sessions will be provided up to 2 times per week, until 12-months corrected age. Intervention sessions will be scheduled based on staffing and caregiver/infant schedules. Session attendance will be monitored and any missed sessions will be rescheduled if possible. Due to the length of the study, it is possible that infants may miss some intervention sessions. Intervention therapists will complete a subjective caregiver survey at the initiation of each session and will appropriately record session outcomes and update appropriate forms in REDCap.

*Activity Playbook*: In addition to the therapist-provided intervention sessions outlined above, caregivers will be provided with an Activity Playbook comprising video and written resources for activities. Completion of these activities will be tracked. If needed, the monitoring mode will be adjusted to fit the needs of the caregiver (e.g., myCap, paper log, phone call). As applicable, intervention therapists will assist in identifying strategies to address any challenges that caregivers may be facing in completing the activities or in achieving or progressing the target dose.

*Toy Kits*: We will provide developmentally appropriate toys to families in the intervention group periodically throughout the intervention phase, to enable families to provide environmental enrichment irrespective of family resources*.* Children in the standard of care group will receive developmentally appropriate toys at the end of their participation in the study, so that each child receives a similar number of toys over the course of the study.

*Mode of Intervention Sessions*: The primary method for intervention delivery will be in-person sessions at the participant’s home or NICU. However, based on the needs of the individual family or infant, sessions may be provided in-clinic (for those in Blocks B or C) or virtually (Blocks A, B, and C); this flexibility will maximize intervention dosage. If sessions are provided in the clinic, families will be reimbursed for parking expenses. Families will be screened for COVID-19 prior to each intervention session. If any member of the family is unwell or there is a known exposure to COVID-19, the session will be rescheduled or conducted via telemedicine.

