*Documentation*: Primary data entry and storage will be completed through the SRAlab REDCap system. Paper surveys and forms will subsequently be added to REDCap by a member of the study team. Intervention forms/surveys may include, but not be limited to: a home environment checklist, demographics, subjective caregiver survey, visit summary, caregiver identified goals, PRIME-SP, PRIME-P (completed monthly by the caregiver(s)), adverse event log, documentation of dosage of caregiver-provided activities from Activity Book and documentation of any additional services received. (See supporting documents for details). Some intervention sessions and assessment sessions will be videoed for training purposes and fidelity checks. Adverse events will be documented and reported to the PI, IRB, and Sponsor, according to IRB guidelines.

*Minimization of risk*: This is a minimal risk study that involves provision of a physical therapy intervention and has no increased risk compared to other standard physical therapy interventions. Several strategies will also be implemented to minimize any potential risk to participants.

- Therapists will adhere to institutional vaccination policies and will self-screen before each intervention or assessment session.
- Intervention therapists and applicable study staff will complete a multi-day training on protocol guidelines and recommendations.
- Medical stability of infant and family readiness to approach will be evaluated prior to beginning the consent process.
- Collaborative communication with caregivers and/or allied health staff and/or medical chart reviews to monitor for any medical status changes or procedure updates within the NICU.
- Tolerance to therapy or assessment procedures will be monitored. If child experiences physiologic or behavioral responses or instability, the therapist will modify the procedures or end the session.
- Any unanticipated adverse event that results in discontinuation of the session will be documented.
- Infant response during intervention sessions will be monitored by the therapist and/or caregiver, and activities will be modified based on infant tolerance.
- Data will be maintained in a secure data capture system, with access limited to those identified as members of the study team.

*Audio/Video Recording*: Video and audio recordings will be used to evaluate the fidelity of intervention delivery and characterize standard of care therapy sessions.

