# Potential Benefits to participants

We cannot guarantee any benefit to participation in the study or proposed intervention. However, infants in the intervention group may benefit from the high-dose, individualized therapy based on scientific evidence and clinical practice. Based on caregiver responses to the monthly parent subjective form, we will attempt to facilitate access recommended services outside of the study for all participants.

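### Adverse events are ascertained more intensively in the intervention arm, so pooled by-arm counts of minor or caregiver-reported events would lean towards that arm through detection alone

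*Protocol*

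**What the plan says.** Under Study Intervention(s), the additional-monitoring paragraph for the intervention arm opens "Intervention therapists and study team members will monitor infant response to intervention sessions", and its list of items includes "any adverse events/changes in medical status, additional services received outside of study participation". The matching paragraph under Standard of Care Group names no therapist: "Study team members will monitor for any adverse events/changes in infant medical status, general medical and health updates". Both paragraphs end with the same sentence: "Surveys or medical chart reviews may be utilized to capture the above information throughout study participation". It is permissive and gives no interval in either arm.

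Only the intervention arm has study therapy sessions. Block A provides one or two a week in the NICU, and the NICU paragraph of Procedures Involved has therapists begin each one by reviewing changes in the infant's status. After discharge the Home paragraph allows up to two a week until 12 months corrected age, and there "Intervention therapists will complete a subjective caregiver survey at the initiation of each session".

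The Documentation paragraph names the adverse event log in a list introduced by "Intervention forms/surveys may include, but not be limited to". Potential Benefits to Participants mentions a form that seems to reach both arms: "Based on caregiver responses to the monthly parent subjective form, we will attempt to facilitate access recommended services outside of the study for all participants". The assessment timeline is the same for everyone.

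**The concern.** How often someone looks or asks affects how many events are recorded. One arm has an additional, frequent and unblinded observer for about a year, and no common adverse event inquiry is fixed for both arms. With equal true harm, the intervention arm would then tend to record more skin irritation, tube problems and illness at home. A real excess of such events could also be dismissed as an artefact of closer observation.

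This matters although no formal harm comparison is planned. The multi-site research section has investigator meetings take up adverse events and decide whether the study continues or stops. Whether an independent body would check that reading is unclear: the section on monitoring for participant safety says that no DSMB is required, while Data Quality Control refers to one reviewing data collection quarterly.

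Analysis cannot repair the problem later. If common questions are not asked and the source of each event is not recorded, comparable caregiver-reported data will not exist.

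**Working it through.** The protocol gives no adverse event rate, detection rate or planned comparison, so there is no figure of its own to reproduce on this point.

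**1. Channels side by side**

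| Channel | Intervention | Standard of care |
| --- | --- | --- |
| Study team monitoring | yes | yes |
| Surveys or chart review (optional, no interval) | yes | yes |
| Scheduled assessments | yes | same schedule |
| Monthly parent form | apparently | apparently |
| Therapist monitoring at NICU sessions | 1-2 per week | none |
| Therapist monitoring and caregiver survey at home sessions | up to 2 per week | none |

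The arms differ only in the last two rows. None of the shared rows has stated adverse event questions or a stated chart-review interval.

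**2. Contact counts**

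- From 3 to 12 months corrected age is about 39 weeks. 39 × 2 = 78 therapist sessions at most, against 0. Each arm also has 3 scheduled assessments (6, 9 and 12 months).
- Over the year from term, assuming discharge at 40 weeks postmenstrual age: 52 × 2 = 104 sessions at full attendance. Shared contacts are 12 monthly forms + 6 assessments (months 1, 2, 3, 6, 9, 12) = 18.
- Ratio of contacts at full attendance: (104 + 18)/18 = 6.8. At half attendance: (52 + 18)/18 = 3.9. At one quarter: (26 + 18)/18 = 2.4.

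The imbalance remains if many sessions are missed. These are ratios of contacts and say nothing directly about detection.

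**3. What unequal detection would do (assumed figures, not in the protocol)**

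Observed proportion = true proportion × detection probability. With equal true risk, the observed risk ratio is therefore the ratio of the detection probabilities. Assume a true risk of 20% in both arms, 90% detection in the intervention arm, and n = 77 per arm (the protocol's evaluable number). The chance of a nominally significant excess in the intervention arm is

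Φ{[p₁ − p₂ − 1.96·√(2p̄(1 − p̄)/n)] / √[p₁(1 − p₁)/n + p₂(1 − p₂)/n]}, where p̄ is the mean of p₁ and p₂.

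| Detection, standard of care | Observed, intervention | Observed, standard of care | Risk ratio | Chance of spurious excess |
| --- | --- | --- | --- | --- |
| 75% | 18% | 15% | 1.2 | 7% |
| 60% | 18% | 12% | 1.5 | 18% |
| 45% | 18% | 9% | 2.0 | 37% |

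With equal detection the ratio is 1.0 and the chance is the nominal 2.5% in that direction. That is the situation for events counted only from sources applied alike in both arms.

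**The case against.** The strongest reply is that the protocol plans no comparison for this bias to distort. Adverse events are not an endpoint or a listed outcome, and the by-arm summaries under Data analysis cover baseline characteristics, outcomes and compliance. How events are tabulated may be left to an analysis plan that is not shown. This stands as to tabulation. It does not answer the point about collection, which is protocol content, nor about the investigator meetings, where counts may be read informally.

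Second, the forms are not reproduced. Nothing shows that the session survey asks about adverse events or that the monthly form does not, so a common source may already exist. That is fair, but the protocol does not commit to one, and therapist monitoring is stated whatever the survey contains.

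Third, more contact is inherent in testing a home-visit programme. That is true, and the remedy does not require equal contact.

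Some stronger readings are tempting and are not supported:

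- A reader might infer that surveys, chart review and assessments are a lesser substitute given only to standard of care. They apply to both arms; the difference is the added therapist channel.
- A reader might infer that standard of care has no adverse event log. The list that names it is open-ended and includes items evidently collected in both arms, such as demographics and additional services. Its placement is ambiguous.
- A reader might take the statement under Risks to Participants, that risk is not significantly increased, as a claim about the randomized arms. It compares the sessions with standard physical therapy sessions, and the trial does not set out to test it.

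**Conclusion.** The point holds in a limited form. Ascertainment is more intensive in the intervention arm, and no arm-neutral adverse event inquiry is fixed. Pooled by-arm counts of minor or caregiver-reported events would therefore tend to be higher in that arm even with no true difference.

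It would go too far to infer that adverse events cannot be compared at all, or that every harm comparison is biased. Death, surgery and readmission can be compared if the same chart review is done in both arms, and so can events elicited in the same way at common assessments or on a common form.

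The size of the bias cannot be derived from the document. The contact ratios of 2.4 to 6.8 assume discharge at term and attendance between one quarter and full. The risk ratios of 1.2 to 2.0 follow directly from the assumed detection rates. The change is worth making because it is cheap and must be made before the data are collected.

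**What to change.** - In the additional-monitoring paragraphs for both arms and in the Documentation paragraph, put the same adverse event and medical-status questions on the monthly parent form, and state that all participants receive it.
- Make the same chart review mandatory in both arms at each common assessment, in place of the present optional wording.
- State that the adverse event log applies to both arms, and record in it the source of each event (monthly form, chart review, assessment or intervention session).
- State that any by-arm reading of adverse events, including at investigator meetings, uses only the common sources. Report events known only from intervention sessions separately, for that arm.

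The cost is some protocol wording, a slightly longer monthly form, and chart review at every common assessment. The comparative count will leave out events known only from sessions, but these are still reported. No visit is added.
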